**3.21 Participant flow**

Figure 3.2 displays the consolidated standards of reporting trials (CONSORT) flow diagram for this study. It will be populated after the trial.

The flow diagram for the study can be represented as shown in the figure below;

**Screening**

Assessed for eligibility (n=No of Household/clusters)

Excluded (n= number of households)

Not Meeting inclusion criteria (n=)

Decline to participate (n=)

Other reasons (n=)

Assessed for eligibility (n=No of Household (clusters))

**Enrolment**

**Iron + Folic Acid:**

**Allocated intervention**

**Cluster (n=)**

**Children (n=)**

**Did not receive**

**Cluster (n=)**

**Children (n=)**

**Iron, Folic Acid Albendazole:**

**Allocated intervention**

**Cluster (n=)**

**Children (n=)**

**Did not receive**

**Cluster (n=)**

**Children (n=)**

**Iron, Folic Acid LAD**

**Allocated intervention**

**Cluster (n=)**

**Children (n=)**

**Did not receive**

**Cluster (n=)**

**Children (n=)**

**Iron, Folic Acid Albendazole LAD**

**Allocated intervention**

**Cluster (n=)**

**Children (n=)**

**Did not receive**

**Cluster (n=)**

**Children (n=)**

**Allocation**

**Loss to follow-up**

**Clusters (n=)**

**Children (n=)**

**Discontinued treatment**

**Clusters (n=)**

**Children (n=)**

Three-month intervention

**Loss to follow-up**

**Clusters (n=)**

**Children (n=)**

**Discontinued treatment**

**Clusters (n=)**

**Children (n=)**

**Loss to follow-up**

**Clusters (n=)**

**Children (n=)**

**Discontinued treatment**

**Clusters (n=)**

**Children (n=)**

**Loss to follow-up**

**Clusters (n=)**

**Children (n=)**

**Discontinued treatment**

**Clusters (n=)**

**Children (n=)**

**Follow-up**

**Analysed**

**Clusters (n=)**

**Children (n=)**

**Excluded from analysis**

**Clusters (n=)**

**Children (n=)**

**Analysed**

**Clusters (n=)**

**Children (n=)**

**Excluded from analysis**

**Clusters (n=)**

**Children (n=)**

**Analysed**

**Clusters (n=)**

**Children (n=)**

**Excluded from analysis**

**Clusters (n=)**

**Children (n=)**

**Analysed**

**Clusters (n=)**

**Children (n=)**

**Excluded from analysis**

**Clusters (n=)**

**Children (n=)**

**Analysed**

Figure 3.2 Consolidated standards of reporting trials (CONSORT) flow diagram for this study

**3.22 Work Plan**

The work plan is prepared based on the proposed methodology is as shown in table 3.3

**Table 3.3: work plan**

|  |  | **Period (Months)** | | | | | | |
| --- | --- | --- | --- | --- | --- | --- | --- | --- |
| **No.** | **Activities** | **1** | **2** | **3** | **4** | **5** | **6** | **7** |
| **1.0** | **Start-up Activities and Document Review** |  |  |  |  |  |  |  |
| 1.1 | Final correction of study protocol |  |  |  |  |  |  |  |
| 1.2 | Desk Review |  |  |  |  |  |  |  |
| 1.3 | Reconnaissance activities |  |  |  |  |  |  |  |
| 1.4 | Development of Management Plan, Training |  |  |  |  |  |  |  |
| **2.0** | **Mobilisation and Preparatory Activities for Field** |  |  |  |  |  |  |  |
| 2.1 | Development of Survey Instruments and related Protocols |  |  |  |  |  |  |  |
| 2.2 | Recruitment of Enumerators |  |  |  |  |  |  |  |
| 2.3 | Training of Enumerators |  |  |  |  |  |  |  |
| 2.4 | Pre-testing of Tools and Skills (Quantitative and Qualitative) |  |  |  |  |  |  |  |
| 2.5 | Finalisation of Tools (and upload on survey platform) and Printing of other instruments and manuals |  |  |  |  |  |  |  |
| 2.6 | Mobilisation/Procurement of Logistics and Equipment |  |  |  |  |  |  |  |
| **3.0** | **Data Collection and Data Cleaning** |  |  |  |  |  |  |  |
| 3.1 | Quantitative Data Collection and Supervision |  |  |  |  |  |  |  |
| 3.2 | Data Cleaning, Editing and Transcription |  |  |  |  |  |  |  |
| 3.3 | Interventions |  |  |  |  |  |  |  |
| **4.0** | **Data Analysis, Reporting and Debriefing** |  |  |  |  |  |  |  |
| 4.1 | Data cleaning and analysis |  |  |  |  |  |  |  |
| 4.2 | Drafting of Report |  |  |  |  |  |  |  |
| 4.3 | Review of First Draft with Comments from Supervisor |  |  |  |  |  |  |  |
| 4.5 | Presentation of Findings at journal club meeting |  |  |  |  |  |  |  |
| 4.6 | Finalised Draft Report with Comments from supervisors and colleagues |  |  |  |  |  |  |  |
| **5.0** | **Submission of Data Reports** |  |  |  |  |  |  |  |
| 5.1 | Submission of Final Report (Hard and Soft Copies) |  |  |  |  |  |  |  |

**3.23 Budget**

The budget for the project is summarised under the following headings: Summary of costing, Fee for staff, administrative and office, transportation and training, Laboratory reagent and equipment use and intervention cost. Table 3.4 displays the budget items.

**Table 3.4.1 Summary of Costing**

| **SUMMARY OF COSTING** |  |  |  |
| --- | --- | --- | --- |
| **COST ITEM** |  | **Rates (USD)** | **GHc** |
| FEES FOR STAFF | cost to be borne by PI | |  |
| ADMINISTRATIVE AND OFFICE COST | cost to be borne by PI | |  |
| TRANSPORTATION AND TRAINING |  | 1210.00 |  |
| LABORATORY REAGENT AND EQUIPMENT USE |  | 3065.00 | 15325 |
| INTERVENTION COST |  | 600.00 | 3000 |
| **TOTAL GROSS BUDGET** | Received funding | **4875.00** | **24375** |

**Table 3.4.2 Supplies**

| **SUPPLIES {LABORATORY REAGENT (base line and post intervention budget for 450 children. excess to take care of controls, calibrations and repeats)}** | | | |  |
| --- | --- | --- | --- | --- |
| **ITEM** | **No.** | **Number of tests** | **Rates (USD) per Each** | **Subtotal (USD)** |
| Full blood count reagents |  |  |  |  |
| Human count diluent | 1.5 | 450 | 76 | 114 |
| HC Lyse | 1.5 | 450 | 90 | 135 |
| HC cleaner | 1.5 | 450 | 64 | 96 |
| Control | 1 | 450 | 160 | 160 |
| Serum Ferritin |  | 450 | 0.9 | 405 |
| Total Iron Binding capacity |  | 450 | 0.9 | 405 |
| Serum Transferin |  | 450 | 0.9 | 405 |
| Serum Iron |  | 450 | 0.9 | 405 |
| Serum Vitamin B12 |  | 450 | 0.9 | 405 |
| Serum Folate |  | 450 | 0.9 | 405 |
| Normal saline | 2 L |  | 2 | 2 |
| Giemsa powder for malaria examination | 12.5 grams |  | 40 | 40 |
| Absolute methanol for malaria and film comment | 1L |  | 5 | 5 |
| Glycerol for malaria examination | 1 L |  | 5 | 5 |
| Leishman Powder for film comment | 12.5 grams |  | 40 | 40 |
| Microscope cover slides | 5 | 1.6 per 100 | 1.6 | 8 |
| microscope slides | 20 packs | 1.5 per pack of 50 | 1.5/50 | 30 |
| **Subtotal** |  |  |  | **3065** |

The minimum sample size of 184. However 200 was used for budgeting to take care of any broken, spilled out syrups that could occur in the administration of the drugs at home. The syrup requirement of an average two and half year old was used in the calculation of the number of bottles of iron and folic acid syrup required by each child.

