Mortality estimates showed that, 5.8 million children lower than five years died in 2015 [10]. Sub-Saharan Africa in 2013 contributed 25% of global births and 50% of global deaths of children under five years which is respectively projected to reach 33% births and 60% deaths by 2030 [11]. Anaemia contributes significantly to deaths within this age group either directly or indirectly by complicating other conditions such as malaria, malnutrition, diarhoea and pneumonia. It has been estimated that for each 1g/dl increase in hemoglobin, the risk of death falls by 24% [12]. Also 1.8 million deaths in children under five within Africa could be avoided by increasing the hemoglobin of these children by 1g/dl.

There is an urgent need to reduce the burden of anaemia in communities within developing countries. This has the potential of improving lives and averting many preventable deaths in children under-five years. Most of the causes of anaemia in children under-five are preventable. Globally, Iron deficiency anaemia is the dominant causes of anaemia accounting for more than 60% of all anaemia [13]. Iron deficiency anaemia in children within developing countries is partly due to increased physiological demands associated with child growth [14] and also, reduced intake complicated by predominantly cereal based diet with high content of phytates, phenols and other ligands that impair iron absorbtion [15]. Increased loss of blood from hookworm infestation has also been estimated to account for a significant proportion of iron deficiency anaemia [16] .

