**1.6.2 Specific Objectives**

1. To determine the baseline prevalence of anaemia and iron deficiency anaemia among children under five years in the Kumbungu district of northern region.
2. To determine factors associated with anaemia among children under five years in the Kumbungu district of Ghana
3. To develop a Locally Available Dietary (LAD) intervention which is culturally acceptable, cost effective and nutritionally appropriate for a behavioural change communication
4. To test the effects of LAD intervention in children aged 6-59 months receiving iron and folic acid for anaemia.

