Anaemia is a widespread public health threat, affecting people of all ages, sex, and of all geographical regions. In the year 2010, the global prevalence of anaemia was estimated at 32.9% [14]. Among children aged five and below, the prevalence of anaemia globally was estimated at 43% in the year 2011 [6]. Severe anaemia is a major causes of sickness and death among children under five in sub-Saharan Africa [32].

- - 1. **Prevalence, Burden and distribution**

Global statistics for anaemia is not published in real time. The most recent publication of the global prevalence of anaemia dates back to a study conducted and published in 2013 which studied global haemoglobin concentration from the year 1995 to 2011 [6, 14]. In that study, the global burden of anaemia was estimated to affect more than 2.2 billion of the world’s population in 2010, thus 32.9%. The age group 0-5 years were most affected with a prevalence of 41.8%. In Africa, more than 60% of preschool children are anaemic [4]. The WHO African region had countries with the lowest haemoglobin levels and highest prevalence of anaemia. Using 2011 data, west Africa and central Africa together has a prevalence of anaemia in children under five years estimated at 71% with severe anaemia accounting for 5% [6]. The mean haemoglobin of children aged less than five years in the global, regional and national trends in haemoglobin study published in 2013 found children from central and West Africa to have the lowest mean haemoglobin concentration among children under five [6]. Significant inequalities exist in the anaemia burden between the wealthiest and the poorest quintiles in Ghana [33] .

- - 1. **Aetiologies of anaemia in children under five**

Majority of anaemia in children can be classified as nutritional anaemia. The most significant nutritional deficiency resulting in anaemia is iron. Almost half of all anaemia is due to iron deficiency anaemia [14]. Second most important cause of nutritional anaemias is vitamin B12 deficiency [34]. Iron is an important substance necessary for almost all living organisms. It forms part of a wide variety of metabolic processes, including oxygen transport, deoxyribonucleic acid (DNA) synthesis, and electron transport [21].

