Certain disease conditions have shown convincing effect on the prevalence of anaemia. Malaria and soil transmitted helminths are the common causes of anaemia of infectious origin among children [26]. The mechanism through which these infections act is by promoting nutrient loss, impairing nutrient absorption and or metabolism. The principal causes of anaemia from parasites include infection from soil transmitted helminths such as hookworm [26]. Heavy hookworm infection can lead to about 5mg per gram of faeces loss of iron. Another parasitic infection which is commonly implicated in blood loss in children and its associated anaemia is schistosomiasis. Schistosomiasis though eventually leads to blood loss, the exact mechanism could include spleen sequestration and hemolysis of red blood cells.

Malaria is the most common infectious cause in sub-Saharan Africa. In the year 2015, about 88% of global malaria case were from sub-Saharan Africa [42, 43]. About 15% of all anaemia in children under five are attributable to malaria [26]. Malaria from *Plasmodium falciparum* is the most cause of anaemia in children under five. The mechanism of causing anaemia is due to haemolysis of red blood cells and suppression of hemopoiesis through the process of upregulation of hepcidin which results in prevention of iron absorption from diet and the redistribution of iron to macrophages resulting in low availability of iron for hemopoisis [44]. Other disease conditions such as HIV infection and Tuberculosis contributes to anaemia.

- - - 1. **Socioeconomic and Environmental determinants**

Socioeconomic factors are strongly linked to anaemia in children under five. Poor socioeconomic status affects nutritional behaviours which contribute to anaemia. Poverty is a factor that affects health seeking behaviour and prevention of anaemia which increases the likelihood of a child becoming anaemic [41]. Also low maternal educational attainment is linked with child anaemia. Mothers with low/ no formal education are more likely to have children who are anaemic [45]. Educational status influences mother’s ability to process nutritional information and provide adequate nutrition for the child [46]. Rural residence is associated with higher prevalence of anaemia due to the often inequity of distribution of social amenities such that resident of urban areas are more likely to have access to services including health facilities, sanitation, water [26].

- 1. **Consequence of Anaemia**

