Data analysis would be by intention to treat and per protocol basis. Descriptive statistics would be used to describe and display a baseline characteristics of study participants by study arms to allow for comparing of the study arm after randomisation. The primary outcomes are the change in mean haemoglobin concentration and change in proportion of iron deficiency calculated from serum iron results for each arm of the study. This would be obtained by computing the mean change in haemoglobin concentration of each study participant within the study arm. A two-sample Student’s t-test assuming equal variances would be performed to test the hypothesis that the resulting mean haemoglobin from the two arms of the study are equal. Change in proportion of anaemic (ie, haemoglobin concentration <110 g/L), severely anaemic (ie, haemoglobin concentration <70 g/L) would be obtained for all groups. Nutritional z scores will be calculated according to the WHO growth reference curves with the use of Epi Info version 7.2.2.2. Weight-for-height, height-for-age, and weight-for-age z scores of less than −2 would be classified as wasting, stunting, and underweight, respectively; z scores of less than −3 would be considered to indicate severe wasting, severe stunting, or severe underweight. Underweight (ie, weight-for-age Z scores less than −2), and wasted (ie, weight-for-height Z scores less than −2); mean prevalence of diarrhoea, dysentery, and acute respiratory infection based on 7-day maternal recall and cumulative mortality would be analysed.

The trial is designed with the sample size and power considerations to detect a 0·2 difference in length-for-age, height for weight Z scores, a reduction of 8 percentage points in stunting, and a 2·6 g/L shift in haemoglobin for the marginal effect of either intervention, with 90% power and type 1 error of 5%. Selected covariates would be entered in a multivariable regression model; a forward stepwise selection procedure would be implemented with p<0·2 to enter. A log-binomial specification would be used to facilitate estimation of Risk Ratios (RR).

Depending on the analysis, other methods for comparison of groups while accounting for within-cluster correlation would include multinomial and ordinal regression models with robust variance estimation.

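### Malaria films are budgeted but never scheduled or analysed, while section 3.20 classifies iron deficiency from serum iron, which on the protocol's own account afebrile malaria may lower (minor)

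*Protocol*

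**What the plan says.** **Budget.** Protocol Table 3.4.2 is headed as covering baseline and post-intervention testing. It lists "Giemsa powder for malaria examination", glycerol and methanol for the same purpose, Leishman stain for film comments, cover slides and 20 packs of 50 slides. The Giemsa line has no test count of its own.

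**Schedule and analysis.** No malaria film is named in the outcome sections (3.12), Table 3.1, the data collection procedure (3.13), the analysis (3.20) or the child data sheet (Appendix 5). Section 3.13 collects morbidity in general terms. The morbidities that 3.20 lists are diarrhoea, dysentery and acute respiratory infection.

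**Iron deficiency.** Section 3.20 names as a primary outcome the "change in proportion of iron deficiency calculated from serum iron results". The abstract, 3.12.1 and Table 3.1 give only haemoglobin and anaemia prevalence as primary. Section 3.12.2.2 also measures ferritin, as the main biochemical marker, and transferrin saturation. Objective 1 is "To determine the baseline prevalence of anaemia and iron deficiency anaemia among children under five years".

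**Malaria.** Section 2.2.3.3 says that malaria leads to "redistribution of iron to macrophages resulting in low availability of iron for hemopoisis" and that "About 15% of all anaemia in children under five are attributable to malaria". Section 3.5.2 excludes infective illness only when there is fever, judged from self-report and records.

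**The concern.** Iron held in macrophages is not circulating, so a child with malaria may have low serum iron while body iron is adequate. The protocol does not state this last step. It is an inference from section 2.2.3.3. A classification based on serum iron alone would count such a child as iron deficient. The test that would identify the child appears in the budget but not in the procedures.

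Two results are exposed. Objective 1 is a single-group estimate, so randomisation gives it no protection and its prevalence may be too high. In the arm comparison, children whose low serum iron comes from malaria can change class for reasons unrelated to diet, which dilutes the change in iron deficiency. Objective 2, "To determine factors associated with anaemia among children under five years in the Kumbungu district of Ghana", is a natural use of a baseline film, but the protocol does not link the two.

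**Working it through.** **1. Does the budget support films?** The Table 3.4.2 lines sum to the stated subtotal: (114 + 135 + 96 + 160) + 6 × 405 + (2 + 40 + 5 + 5 + 40 + 8 + 30) = 505 + 2,430 + 130 = USD 3,065. Malaria and film supplies account for 40 + 5 + 5 + 40 + 8 + 30 = USD 128. Slides number 20 × 50 = 1,000. One malaria film and one film comment for each of the 450 budgeted tests would need 900. The purchase is large enough for two rounds, but the table does not assign films to each round.

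**2. Inputs for the size of the error**
- Anaemia prevalence a = 0.82 (section 3.7).
- True iron deficiency as a share of anaemia, p: 0.50, from "Almost half of all anaemia is due to iron deficiency anaemia" (section 2.2.2), or 0.60, from "accounting for more than 60% of all anaemia" (section 1.1). The two sections differ, so both are shown.
- Malaria share of anaemia, m: 0.15 from section 2.2.3.3. That figure is an attributable share, not parasitaemia measured in this district, and excluding febrile children could lower it. An assumed lower value of 0.05 is therefore shown too.
- Assumption: every malaria child has low serum iron. This makes the results a ceiling.

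**3. Denominator.** Enrolled children are all anaemic (section 3.5.1.2), so objective 1 must be computed on screened children. Screened: 184 / 0.82 = 224.4, taken as 225.

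**4. Inflation in percentage points of all screened children**

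Independence: a × m × (1 − p). No overlap: a × m.

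| p | m | Independence | No overlap |
|---|---|---|---|
| 0.50 | 0.05 | 0.82 × 0.05 × 0.50 = 2.1 | 0.82 × 0.05 = 4.1 |
| 0.50 | 0.15 | 0.82 × 0.15 × 0.50 = 6.2 | 0.82 × 0.15 = 12.3 |
| 0.60 | 0.05 | 0.82 × 0.05 × 0.40 = 1.6 | 4.1 |
| 0.60 | 0.15 | 0.82 × 0.15 × 0.40 = 4.9 | 12.3 |

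**5. Sampling error for comparison.** True prevalence is 0.82 × 0.50 = 0.41 or 0.82 × 0.60 = 0.492. With n = 225 and the design effect of 1.03 from section 3.7:
- 1.96 × √(0.41 × 0.59 × 1.03 / 225) = 0.065
- 1.96 × √(0.492 × 0.508 × 1.03 / 225) = 0.066

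The 1.03 covers household clustering only. Sampling a few communities could widen the interval.

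**6. Children involved.** At m = 0.15, 0.15 × 184 = 27.6, about 14 per arm. A film-negative subset would keep 0.85 × 184 = 156.4, about 156.

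**The case against.** **Serum iron may be shorthand for the panel.** Section 2.6 speaks of serum iron studies just after listing ferritin, transferrin saturation and transferrin receptors, and the budget buys ferritin, iron-binding capacity and transferrin. The phrase in 3.20 may mean all of these, and a full case definition could sit in an SAP. This stands as a possibility. Read literally, though, 3.20 fixes the classification on serum iron and gives no ferritin rule, so the wording needs correcting either way.

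**The mechanism is partial.** Section 2.2.3.3 also attributes malarial anaemia to haemolysis, which on the protocol's account need not lower serum iron. This stands, and it is why the figures are a ceiling.

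**Table 3.1 is not exhaustive.** It also omits head circumference, skinfolds and blood-count indices, so absence from it is weak evidence alone. But no other procedure or analysis section names the film, and scheduling a specimen examination is not normally left to an SAP. Using malaria as a covariate for objective 2 could be left there.

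**Readings that go too far.** A reader might infer that the trial's comparison is biased. Randomisation balances malaria on average, so neither arm is favoured. A reader might also infer that the primary outcome is misclassified. Only 3.20 gives iron deficiency that status, and malaria does not change how haemoglobin or anaemia is classified. Expressing the error as a share of the 184 anaemic children gives 2 to 15 points, but that is not the prevalence objective 1 asks for.

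**Conclusion.** The point holds as a minor one. Malaria films are budgeted without a place in the schedule or analysis, and the literal serum-iron rule in 3.20 could count some children with afebrile malaria as iron deficient.

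The ceiling on the resulting inflation of objective 1 is about 1.6 to 6.2 points under independence and 4 to 12 points with no overlap, against a half-width of about 6.5 points. Only the no-overlap case at the 15% share clearly exceeds sampling error. These figures rest on every malaria child having low serum iron, on a 5% to 15% share, and on the inferred link from macrophage iron to serum iron. Dilution of the change in iron deficiency is expected in direction but has not been quantified.

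That films were meant for both rounds is implied by the table heading and the slide count, not stated.

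**What to change.** 1. Add a malaria film to Table 3.1 at week 0, and at week 12 for description only.
2. Report baseline iron deficiency anaemia on all screened children and the change in iron deficiency on all enrolled children, each with a supporting analysis in children film-negative at week 0. Do not select on week-12 status, which is post-randomisation.
3. State in 3.20 that the classification uses the ferritin and transferrin saturation already measured, not serum iron alone, and bring the outcome's status into line with 3.12.1 and Table 3.1. The protocol does not describe how malaria affects these markers, so the film-negative analyses are still needed.
4. State that film-positive children are referred for standard care. Their treatment is not in the budget.

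**Cost.** No extra visit or blood draw is needed. Tests come to 225 + 184 = 409 of the 450 budgeted. With one slide per malaria film and a film comment at week 0, slides come to 225 + 225 + 184 = 634 of 1,000. With two slides per malaria film they come to 2 × 225 + 225 + 2 × 184 = 1,043, which is one more pack at USD 1.50. The real costs are film-reading time and a smaller supporting subset (about 156 of 184 enrolled children at a 15% share).
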